## Abstract

**Introduction:**

Large-vessel occlusion (LVO) stroke is effectively treated by time-critical thrombectomy, a highly specialised procedure only available in a limited number of centres. Many patients with suspected stroke are admitted to their nearest hospital and require transfer to access treatment, with resulting delays. This study is evaluating the accuracy of a new rapid portable test for LVO stroke which could be used in the future to select patients for direct admission to a thrombectomy centre.

**Methods and analysis:**

Rapid Assay Diagnostic for Acute Stroke Recognition (RADAR) is a prospective observational cohort study taking place in stroke units in England. Participants are adults with a new suspected stroke with at least one face, arm or speech (FAST) symptom(s) and known onset within 6 hours or last known to be well 6–24 hours ago. The index test (‘LVOne test’ (Upfront Diagnostics)), consists of two portable lateral flow assays which use fingerprick capillary blood to detect d-dimer and glial fibrillary acidic protein concentrations. Reference standards comprise independently adjudicated standard CT/MRI brain±CT/MR angiography with senior clinician opinion to establish: ischaemic stroke±LVO; intracerebral haemorrhage; transient ischaemic attack; stroke mimic. Analyses will report sensitivity, specificity and negative and positive predictive values for identification of LVO stroke. Powered using a primary analysis population (≥2 FAST symptoms and known onset within 6 hours), 276 participants will detect a test specificity of 92%. The broader total study population which allows evaluation of the test for milder symptoms and unknown onset times is estimated to be 552 participants.

**Ethics and dissemination:**

Ethical (North East—Newcastle & North Tyneside 2 Research Ethics Committee (reference: 23/NE/0043), Health Research Authority and participating National Health Service Trust approvals are granted. Consent is required for enrolment. Dissemination of results will include presentations at conferences, publication in journals and plain English summaries.

**Trial registration number:**

ISRCTN12414986.

STRENGTHS AND LIMITATIONS OF THIS STUDYThis is a real-world diagnostic accuracy study involving participants representative of the prehospital suspected stroke population where the new test would be deployed in the future.The study has been designed to minimise selection bias and facilitate inclusion via the use of several invitation and consent options which cover incapacity, rapid discharge and death.A standardised approach to assign ‘gold-standard’ reference standard outcomes is used to support reproducibility of the data obtained.While hosting the study in hospitals may not truly reflect ambulance use of the test, this locality will provide robust data for diagnostic accuracy and it avoids the substantial challenges that arise when conducting research spanning both the prehospital and hospital settings.

## Introduction

 Stroke caused by cerebral ischaemia (85%) or haemorrhage (15%) affects around 13.7 million people across the world each year and causes a large burden of mortality and morbidity.^1^ In the UK alone, there are around 113 000 new strokes each year.^2^ Where ischaemic stroke is caused by occlusion of a large intracranial blood vessel (approximately 30% of ischaemic stroke),^3^ outcomes can be significantly improved by time-critical intra-arterial mechanical thrombectomy.^4 5^ This is a highly specialised procedure involving inserting an arterial catheter under X-ray guidance to extract the blood clot causing the stroke and can only be performed in appropriately resourced hospitals.

In the UK, there over 100 hospitals, which provide standard care for stroke patients (eg, thrombolysis) but only 24 of these centres are also able to undertake thrombectomy.^6 7^ As most patients with suspected stroke present to ambulance services which currently convey to the nearest hospital providing stroke care,^8^ onward transfer to a thrombectomy centre is required for many of the people suitable for treatment. National audit data from 2022/2023 demonstrate that it takes an average of over 3 hours from arrival at a first hospital to arrival at a thrombectomy centre.^9^ Similar delays to accessing thrombectomy are seen in other healthcare systems across the world.^10 11^

Direct admission of all suspected stroke patients to thrombectomy capable centres might decrease treatment delays but this is not typically considered a suitable service model for the UK.^6 7^ Capacity is limited but also many patients would not receive a diagnosis of large-vessel occlusion (LVO) stroke after investigation and therefore could be more appropriately treated in a local centre. This is because up to 40% of people suspected to be having a stroke by prehospital ambulance practitioners receive a non-stroke ‘mimic’ diagnosis after hospital assessment^12^ and only approximately 30% of ischaemic stroke are due to LVO.^3^

An alternative approach to facilitate timely access to thrombectomy treatment is to identify people likely to have LVO stroke prehospital and selectively redirect these individuals to a treatment centre.^13^ However, for this option to be feasible, a method of rapid and accurate LVO recognition in the prehospital setting is required. While there has been considerable interest in using prehospital symptom scale scores for this purpose, there are concerns about their real world accuracy when used in isolation.^13^

Recent work using biobank samples of venous blood drawn from suspected stroke patients in the emergency department within a mean of 2.6 hours from symptom onset indicated that combining blood concentrations of d-dimer and glial fibrillary acidic protein (GFAP) with clinical symptom scale scores (eg, Face Arm Speech Test (FAST), Field Assessment Stroke Triage for Emergency Destination (FAST-ED)) gave high area under the receiver operator curve (AUC) values for prediction of LVO stroke.^14^ When combining d-dimer and GFAP with the FAST, which is the symptom scale most commonly used by UK ambulance practitioners, the AUC was 0.93 with optimal specificity of 93% and sensitivity of 78%.^14^

These data led to the development of portable lateral flow assays to detect d-dimer and GFAP from fingerprick capillary blood, where results are available within 15 min (together named ‘LVOne test’: Pockit Diagnostics trading as Upfront Diagnostics). Using these lateral flow assays with existing biobank samples demonstrated that a specificity of 92% and sensitivity of 62% for LVO identification could be achieved from the combination of a positive d-dimer line, negative GFAP line and clinical symptom FAST score of 2 or 3 (unpublished data). The assays have been optimised for specificity because the future intended use of the measurements is prehospital triage for redirection whereby high specificity (ie, few false positives) is important to avoid inappropriate transfers.

As the next stage in the evaluation of the LVOne test, a diagnostic accuracy study using prospectively collected samples is being conducted. This manuscript describes the study protocol. Although the future intended purpose of the assays is prehospital use, this study is testing suspected stroke patients rapidly after hospital arrival. This provides a near identical population and avoids the substantial challenges which arise when conducting research spanning the prehospital/hospital setting such as the requirement for multiple testing devices (ie, for placement in all ambulances serving a region), training geographically dispersed ambulance personnel and linking prehospital and hospital patient data.

## Methods and analysis

### Study objectives

The primary objective is to determine the diagnostic accuracy of the LVOne test (using fingerprick capillary blood) for identification of LVO stroke.

Data-driven exploratory objectives may include examination of relationships between the diagnoses that constitute the suspected stroke population, blood biomarker values and key clinical variables (eg, stroke symptoms).

### Study design

The study design is a prospective observational cohort study.

### Study setting

The study is taking place within UK National Health Service (NHS) hospitals with established Hyperacute Stroke Units receiving direct ambulance admissions of patients with suspected stroke.

### Study population

Trained hospital staff (eg, research nurses, research trained doctors) undertake the LVOne test on patients who fulfil the following criteria:

#### Inclusion criteria

Arrived at the study hospital by emergency ambulance.Aged 18 years or over.New acute stroke suspected by ambulance personnel before hospital arrival.At least one FAST symptom, ie, FAST score ≥1 (as determined by hospital staff).Stroke symptoms are known to have begun within the last 6 hours OR the patient was last known to be well between 6 and 24 hours ago (times determined by hospital staff).Blood sampling can be undertaken prior to any reperfusion treatment.Routine brain imaging is intended to be urgently performed.

#### Exclusion criteria

Already assessed at another hospital and ambulance admission is a transfer for continuing care.Assigned a recent previous (within the last 4 weeks) diagnosis of deep vein thrombosis, pulmonary embolism, arterial embolism, stroke, transient ischaemic attack (TIA), long bone fracture, major trauma, any surgery under general anaesthesia (these diagnoses may result in elevated d-dimer).Suffered a recent previous (within the last 4 weeks) head injury which led to hospital attendance (this event may have resulted in elevated GFAP).Stroke symptoms are known to have begun greater than 6 hours ago.

### Participant identification and consent

Patients are assessed for study suitability immediately after arrival at hospital in parallel with their urgent clinical assessment. If a patient is considered to fulfil the eligibility criteria and staff trained about the study are in attendance, the LVOne test is undertaken following a short verbal explanation. A formal research consent process is not undertaken at this time to avoid delays to time-critical treatments.

Once emergency assessments and treatments are completed, all patients who have had the LVOne test are approached for study enrolment. Six different options for study invitation and consent are used to ensure that all tested patients can be potentially recruited. Similar methods have been used by the study investigator team in previous projects.^15 16^

#### Inpatient approach

##### Patients with mental capacity

For patients with capacity to consent to research, a trained member of the hospital staff will approach the patient to discuss the study, provide a standard patient information sheet and subsequently obtain consent in writing. If a potential participant is due to be discharged and wishes to have longer to consider the information before making a decision, a study postal consent form and prepaid reply envelope are issued. Telephone follow-up can be undertaken if the consent form is not returned, including the option to take consent verbally.

##### Patients with mild communication difficulties

For patients with mild communication difficulties due to the effects of stroke or a non-stroke mimic condition on the use and understanding of language (aphasia), a set of ‘easy access’ study documentation will be used. For people due to be discharged and requiring more time to consider participation, an early discharge ‘easy access’ postal consent form can be used, and/or the option to return later for a face-to-face consent discussion.

##### Patients lacking in mental capacity, personal consultee

It is anticipated that approximately one-third of study eligible patients will be unable to engage in an informed consent process due to the effects of stroke and non-stroke mimic conditions on communication and cognition. As exclusion of patients unable to engage with consent would reduce the clinical relevance of the study, enrolment via personal or nominated (professional) consultees is also used.

If a personal consultee can be identified, a discussion about the study is held, a personal consultee information sheet is provided and a consultee declaration form is subsequently completed. Initial discussion can be face to face or via the telephone according to availability, and the declaration form may be completed in person, via post or verbally.

##### Patients lacking in mental capacity, nominated consultee

For patients where a personal consultee cannot be identified, a nominated (professional) consultee is used with a nominated consultee information sheet and declaration form.

##### Early mortality

The early mortality rate following acute stroke is approximately 10% and some non-stroke mimic conditions are also associated with a high mortality, for example, severe infections. LVO stroke typically presents with more severe symptoms and some people with this type of stroke die rapidly following hospital admission. As the exclusion of patients who die soon after admission (and the LVOne test) would reduce the clinical relevance of this study, if a patient dies before consent can be obtained using one of the approaches described above, the local hospital investigator may complete an early mortality declaration form for study enrolment.

### Approach after discharge/transfer

Patients who are discharged from hospital before the consent process can be undertaken are invited to take part by post. An invitation letter, postal patient information sheet and postal consent form are used. Telephone follow-up can be undertaken if the consent form is not returned, including the option to take consent verbally.

### LVOne test (index test)

The LVOne test consists of two portable lateral flow immunoassays. Assay 1 detects d-dimer concentration and assay 2 detects GFAP concentration. When a sample of blood is added to an assay test strip, the target protein (ie, d-dimer or GFAP) is bound by an antibody which is conjugated to a nanoparticle. Following the addition of a reaction buffer, the target protein/antibody/nanoparticle complex flows through the test strip and binds with a second antibody forming a ‘sandwich’ which becomes visible as a coloured line according to the concentration of the target protein.

The d-dimer assay is semiquantitative where the intensity of the line colour is proportional to the concentration of d-dimer in the blood. The GFAP assay is qualitative and the presence of any visible line indicates that GFAP is present in the blood. A positive LVOne test is defined as a visible d-dimer line with an intensity score ≥4 out of 10 points established using a reference scorecard, and an absent GFAP line.

The steps to perform the LVOne test are shown in figure 1.

**Figure 1 F1:**
[figure not shown]
Performing the LVOne test.

### Reference standards (comparator)

Reference standards are required for key clinical outcome states which constitute the suspected stroke population: intracerebral haemorrhage, ischaemic stroke with LVO, ischaemic stroke without LVO, TIA and non-stroke mimic conditions.

Brain imaging tests are available which objectively confirm any intracerebral haemorrhage (CT) and ischaemic stroke with LVO (CTA/MRA). However, for ischaemic stroke without LVO, TIA or mimic conditions, no brain imaging or other diagnostic test alone exists, and for these cases, both the diagnosis assigned by a senior clinician at the participating hospitals and brain imaging findings will be reviewed to assign an outcome state. Full details are provided below and a similar approach has been used by the study investigator team in previous research.^16^

In keeping with routine practice for suspected stroke patients, it is anticipated that all participants in this study will undergo at least one brain imaging test. For the purposes of this study, all routine imaging performed within 72 hours of admission will be reviewed by an experienced consultant neuroradiologist blinded to clinical information and the LVOne test result.

#### Neuroimaging defined clinical outcome states

##### Intracerebral haemorrhage

Intracerebral haemorrhage will be the clinical outcome state assigned if a small (approximately <30 mL), medium (approximately 30–59 mL) or large (approximately ≥60 mL) volume haematoma is recorded during CT (and/or MRI) review by the blinded neuroradiologist.

##### Ischaemic stroke with LVO

Ischaemic stroke with LVO will be the clinical outcome state assigned if CT or MR angiography has been conducted and demonstrates reduced filling in any large branch of the anterior or posterior cerebral circulation. This will be recorded by the blinded neuroradiologist, with use of the 10-Point Clot Burden Score^17^ for the anterior circulation. Angiography is not routinely performed for all suspected stroke patients as clinical or other radiological investigations can exclude the need for this test, for example, plain CT has shown a haemorrhage or another radiological diagnosis for the acute symptoms such as a tumour.

### Other clinical outcome states

Because diagnoses recorded in medical records can vary according to the taxonomy used and the terminology preferred by individual clinicians (eg, chest infection may be used synonymously with pneumonia, bronchopneumonia and lower respiratory tract infection), local hospital clinicians will be asked to select a ‘definite’ or ‘probable’ primary clinical diagnosis according to a predefined framework.^15 16^ As diagnoses are sometimes uncertain for a time after admission to hospital, senior clinicians will be asked to provide a diagnosis assigned at 72 hours after hospital admission (or discharge/death if sooner).

#### Ischaemic stroke without LVO

Ischaemic stroke without LVO will be the clinical outcome assigned if the clinician considered the patient to have a ‘definite’ or ‘probable’ ischaemic stroke and CTA/MRA read by the blinded neuroradiologist confirms the absence of LVO.

#### Ischaemic stroke with unknown LVO status

There are likely to be participants with a clinical diagnosis of ischaemic stroke who have not undergone CTA/MRA for some reason. This may be due to the clinical situation (eg, agitation) or local hospital policies about access to this procedure. In these cases, the LVO status is unknown and a separate clinical outcome ‘ischaemic stroke with unknown LVO status’ will be assigned.

#### Transient Ischaemic Attack

Transient Ischaemic Attack will be the clinical outcome assigned if the clinician records any ‘definite’ or ‘probable’ TIA diagnosis using the predefined framework and brain imaging read by the blinded neuroradiologist does not contain findings which refute this opinion or indicates the presence of one of the other acute outcomes. Following resolution of any data discrepancies (see also below), if there remains any disagreement between blinded neuroradiological review of imaging performed and a clinical diagnosis of TIA, the imaging diagnosis will be used to determine the outcome.

#### Non-stroke mimic condition

A non-stroke mimic condition will be defined as present if the clinician records any ‘definite’ or ‘probable’ non-stroke/non-TIA diagnosis using the predefined framework and brain imaging read by the blinded neuroradiologist is compatible (eg, tumour) and does not contain findings which refute the opinion or indicates the presence of one of the other acute outcomes. Following resolution of any data discrepancies (see also below), if there remains any disagreement between blinded neuroradiological review of imaging performed and a clinical diagnosis of mimic condition, the imaging diagnosis will be used to determine the outcome.

### Assigning the clinical outcome state

The clinical outcome state will be assigned by a separate independent senior stroke clinician who will be blinded to LVOne test result. This clinician will review routine healthcare information collected for the study including the local clinician diagnosis and hospital routine imaging reports, and blinded neuroradiologist reports. A check for discrepancies in the information will first be performed (eg, routine hospital imaging reports are inconsistent with the blinded neuroradiology report, local clinician assigned diagnosis is inconsistent with imaging findings) and as required, data will be queried with the appropriate hospital team. Following any necessary resolution, a clinical outcome will subsequently be assigned according to the descriptions above. If any discrepancies cannot be satisfactorily addressed such that the independent clinician is able to assign a clinical outcome state, the case will be discussed by a Diagnostic Adjudication Committee. The committee will review anonymised clinical information plus the study blinded neuroradiologist report to agree on an outcome state. If the committee cannot reach a consensus, a decision that a clinical outcome state cannot be assigned will be taken.

The predefined diagnosis framework to be used by local hospital clinicians contains an ‘unclear’ option. If this option is selected, the case will also undergo discussion by the Diagnostic Adjudication Committee. If a consensus is reached about a primary diagnosis, a clinical outcome state will subsequently be assigned according to the descriptions above. If a consensus diagnosis cannot be agreed, it will not be possible to assign a clinical outcome state.

Figure 2 shows a decision tree for assigning the clinical outcome state.

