### Sample size

As the intended purpose of the LVOne test is to ‘rule-in’ patients with LVO stroke, the study sample size calculation is based on demonstrating test specificity.

The sample size calculation is based on a ‘primary analysis population’ which consists of patients scoring 2 or 3 on the FAST clinical symptom scale who are also known to be within 6 hours of symptom onset. This is the population where previous data supports high test accuracy and is, therefore, the most likely future use case for the test, ie, the LVOne test would be deployed if an initial routine FAST test conducted by ambulance practitioners indicates a score of 2 or 3, and the patient is within 6 hours of symptom onset. Considering this primary analysis population, using an estimated prevalence of LVO of 32%, a minimum specificity of 80%, alpha=0.05 and beta=0.1, 123 participants are required to detect a specificity of 92% for LVO versus all other clinical outcomes in the study population.

Due to the nature of this clinical study being conducted in NHS hospitals, some enrolled participant’s data may not be complete for inclusion in the primary analysis, for example, it is not possible to assign a patient as LVO present or absent due to the nature of brain imaging undertaken (see also Reference standards section above). This lack of data is hard to estimate as individual hospital policies vary, however, based on assessment of likely available data from each proposed participating site, the primary analysis population sample size has been initially inflated to 276. During the study, there will be regular monitoring of the number of cases which can contribute to the primary analysis and fewer or additional participants will be sought accordingly.

The population being enrolled in the study is broader than the primary analysis population (as described in the Study population section above) and will include people suspected to be stroke by ambulance practitioners with a score of 1, 2 or 3 on the FAST clinical symptom scale and who are also either known to be within 6 hours of symptoms commencing or last known to be well between 6 and 24 hours ago. This broader study population has been chosen to allow for a number of other important analyses (see also Statistical analysis section below) including:

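### A patient whose blinded angiogram shows no LVO can be left without an outcome state when no diagnosis is agreed, although LVO absence is all the specificity analysis needs to know

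*Protocol article*

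**What the plan says.** The Sample size section of the protocol article sets a binary target: "123 participants are required to detect a specificity of 92% for LVO versus all other clinical outcomes in the study population".

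The outcome-state sections do not treat the two sides of that target alike. The LVO state rests on imaging: "Ischaemic stroke with LVO will be the clinical outcome state assigned if CT or MR angiography has been conducted and demonstrates reduced filling". Intracerebral haemorrhage also rests on imaging, since it applies when a "volume haematoma is recorded during CT (and/or MRI) review by the blinded neuroradiologist". Ischaemic stroke without LVO has two conditions: "the clinician considered the patient to have a ‘definite’ or ‘probable’ ischaemic stroke and CTA/MRA read by the blinded neuroradiologist confirms the absence of LVO". TIA and mimic also start from the clinician's diagnosis; for mimic, "A non-stroke mimic condition will be defined as present if the clinician records any ‘definite’ or ‘probable’ non-stroke/non-TIA diagnosis".

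The section on assigning the clinical outcome state has two routes that end with no state. For discrepancies that the independent clinician cannot settle: "If the committee cannot reach a consensus, a decision that a clinical outcome state cannot be assigned will be taken". For cases where the local clinician chose the unclear option: "If a consensus diagnosis cannot be agreed, it will not be possible to assign a clinical outcome state". Neither sentence makes an exception for a patient whose angiography result is known.

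The Blinding section states that the neuroradiologist and the independent stroke clinician are blinded to the LVOne result, and that hospital clinicians are not.

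**The concern.** The 2×2 table needs one fact from the reference standard: whether LVO is present. Where angiography was done and read blind, that fact is available whether or not anyone can separate a small stroke from a TIA or a mimic. The assignment rules make the LVO-absent side depend on that separation all the same. A patient with a clean CTA and no agreed diagnosis has no state, and so appears to belong neither to LVO nor to the other outcomes. This is a different group from ischaemic stroke with unknown LVO status, where angiography was not done.

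Three things are at stake. Evaluable non-LVO patients may be lost from specificity, the measure on which the study is sized. Positive predictive value may shift if LVO patients are not lost in proportion. And the loss may not be independent of the index test: a clinician who has seen a positive LVOne result and a negative angiogram could be more inclined to choose unclear, and such patients are the false positives. The document does not show that this happens, but its rules leave the path open.

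**Working it through.** **1. What each state requires**

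| State | Imaging condition | Clinical diagnosis needed? |
|---|---|---|
| Ischaemic stroke with LVO | Positive CTA/MRA | No |
| Intracerebral haemorrhage | Haematoma on blinded CT/MRI | No |
| Ischaemic stroke without LVO | Negative CTA/MRA | Yes |
| Ischaemic stroke, LVO status unknown | No CTA/MRA | Yes |
| TIA | Nothing that refutes it | Yes |
| Mimic | Compatible, nothing that refutes it | Yes |

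**2. Angiogram-negative patient, diagnosis unclear, no committee consensus.** The LVO and haemorrhage states do not apply. The other states lack the diagnosis they need, and the unknown-status state does not fit because angiography was done. The tie-break that lets imaging prevail (TIA and mimic sections) applies when a recorded TIA or mimic diagnosis conflicts with imaging. Here there is no such diagnosis, and a clean angiogram supplies no positive imaging diagnosis. Result: no state, with LVO known to be absent.

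**3. Angiogram-positive patient, diagnosis unclear or in dispute.** The LVO section gives a state from imaging. The assignment section, read literally, sends any unclear case to the committee and allows it to end with no state. The two passages do not agree.

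**4. The plan's own figure.** Inputs from Sample size: specificity 92% against 80%, alpha 0.05, beta 0.1, LVO prevalence 32%. With an arcsine one-sample test, two-sided:

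n(non-LVO) = [(1.960 + 1.282) / (2·asin√0.92 − 2·asin√0.80)]² = 83.95, and 83.95 / 0.68 = 123.5.

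This matches the stated 123 within rounding. So about 84 non-LVO patients (123 × 0.68 = 83.6) are planned, with about 7 false positives (0.08 × 83.6 = 6.7).

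**5. Illustration.** Assume 5 of the 84 are left unassigned; the document gives no number.
- All 84 kept: 77/84 = 91.7%.
- The 5 lost include 2 false positives: 74/79 = 93.7%.
- The 5 lost include none: 72/79 = 91.1%.

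**6. General form.** Let u be the share of non-LVO patients lost and s the specificity among them (both assumed). Apparent specificity = (0.92 − u·s)/(1 − u).

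| u | s = 0.80 | s = 0.92 | s = 1.00 | Non-LVO n |
|---|---|---|---|---|
| 5% | 0.926 | 0.920 | 0.916 | 80 |
| 10% | 0.933 | 0.920 | 0.911 | 76 |
| 20% | 0.950 | 0.920 | 0.900 | 67 |

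**7. Positive predictive value.** Take sensitivity 62% (Introduction), u = 10%, s = 0.92 and no loss of LVO patients. Apparent prevalence is 0.32/(0.32 + 0.68 × 0.90) = 34.3%. PPV moves from 0.1984/(0.1984 + 0.0544) = 0.785 to 0.1984/(0.1984 + 0.0490) = 0.802, although specificity is unchanged.

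**The case against.** A reader might infer that known non-LVO patients, and only these, drop out, so that the loss is strictly one-sided. The document does not support that. Haemorrhage is a known non-LVO state that imaging fixes, so not every non-LVO patient is exposed. Patients with neither angiography nor an agreed diagnosis also get no state, and their LVO status is not known. Both no-state routes, read literally, reach angiogram-positive patients; one listed example of a discrepancy is disagreement between the hospital and blinded imaging reports, which could concern the occlusion itself.

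A reader might also infer that specificity will be inflated. That does not follow. Step 6 gives a shift in either direction, or none, depending on test performance in the lost patients. No passage says the test does worse where the diagnosis is hard to agree. The 2 false positives among 5 in step 5 are five times the planned 8% rate, and the shifts there (−0.6 to +2.0 points) are small beside a 95% interval of about ±6 points on 84 patients.

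Removal from the 2×2 table is itself an inference. The list of possible exclusions under Statistical analysis is open-ended and does not name unassigned cases. The example of incomplete data under Sample size turns on imaging, which sits close to the rule proposed below. Analysis populations are left to an SAP that is not shown, and the Figure 2 decision tree could not be read. The group may also be small, since probable diagnoses are accepted, sites are queried and a committee follows.

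All of this limits the claim about bias. It does not remove the stated assignment rule, which denies a state to a patient whose LVO status is known.

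**Conclusion.** The point holds as a gap between the assignment rules and the binary target. An angiogram-negative patient without an agreed diagnosis has no state, and no other rule in the article supplies one. It is a strong inference, not a statement in the protocol, that such a patient leaves the specificity analysis. The loss probably falls mainly on the non-LVO side, because only states on that side need a clinical diagnosis, but the conflict between the LVO rule and the no-state rule prevents a firmer statement. Dependence on the index test is possible and not shown. The figures in steps 5 to 7 rest on assumed frequencies and assumed test performance; they are neither estimates nor bounds. The correction is justified because it keeps evaluable patients and closes an avoidable selection path at almost no cost.

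**What to change.** For the primary 2×2 analysis, define LVO status (present, absent, unknown) as its own variable, taken from the blinded CTA/MRA read and set independently of the multi-state diagnosis. A negative read counts as LVO-absent and a positive read as LVO-present, even where the diagnosis stays unclear or the committee does not agree. Limit this to reads that are not themselves in dispute: send to the committee, or class as unknown, only cases where the angiography finding is missing or contested. Patients without angiography who already have an agreed haemorrhage, TIA or mimic state keep their present handling. Reserve the unassigned category for diagnosis-level analyses, and reconcile the LVO section with the assignment section so that they say the same about angiogram-positive patients. Report how many participants had known LVO status but no agreed diagnosis, by LVOne result.

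The cost is one rule in the assignment procedure and the SAP. It uses a read already collected and needs no added patients or procedures. It also avoids recruiting replacements for patients who were evaluable.
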